
#### Effects of RLI clearance on acetabular development: a retrospective and prospective multicenter randomized controlled study

2.2.2.

##### Selection of participants for the retrospective study

2.2.2.1.

To maximize the use of the peak ossification potential of acetabular cartilages in patients before the age of 5 years, pediatric patients who underwent successful closed reduction between 6 and 18 months that had experienced RLI and were ≤5 years old at follow-up were selected as study participants, given that it is more instrumental to observe the reversibility of delayed acetabular cartilage ossification. The frontal pelvic radiographs and MRI images of the hip joint were taken during follow-up to evaluate limbus inversion. The trail is illustrated in a flowchart as shown in Figure 5.

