## Abstract

Closed reduction is a common treatment method for developmental dysplasia of the hip (DDH) in children aged 6–18 months. Residual acetabular dysplasia (RAD) is the most common complication associated with closed reduction. Residual limbus inversion (RLI) is a common condition following DDH closed reduction. Previously, we confirmed that when limbus inversion exceeds 32.2% of the acetabular depth after closed reduction, RLI persists and leads to RAD; however, this was based on a small cohort with a short-term follow-up period. The long-term fate of RLI and the correlation between RLI and RAD have yet to be verified. Therefore, this multicenter clinical study protocol was designed in three parts to investigate the effect of RLI on acetabular development after closed reduction of DDH (a multicenter retrospective cohort study), effect of RLI clearance on acetabular development (a multicenter retrospective and prospective randomized controlled study), and influence of inverted limbus clearance on acetabular development during DDH reduction (a multicenter prospective cohort study). Statistical analysis was performed by assessing the basic measures of acetabular development including the acetabular index and central-edge angle using frontal pelvic radiographs; the magnitude of limbus inversion, cartilaginous acetabular index, and T1ρ mapping values were measured using magnetic resonance imaging. The multicenter retrospective cohort studies required 5 years of follow-up period at minimum, and the prospective randomized controlled studies required reviews of frontal pelvic radiographs every 6 months as well as data pooling every 2 years to compare the short- and mid-term outcomes of hip joint morphological development between the two groups of pediatric patients. This research program is expected to verify that RLI following closed reduction of DDH can affect acetabular development and that limbus excision during DDH reduction can improve postoperative RAD. Therefore, the indication and timing of surgical intervention for RLI after closed reduction of DDH provide a basis for revising the acceptable criteria for utilizing closed reduction of DDH to reduce the incidence of osteoarthritis caused by RAD following DDH treatment.

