### Objectives

2.1.

Limbus inversion is a common pathological change in DDH; however, how does the RLI evolve after closed reduction, and how does it affect development of the acetabulum? To date, there have been no reports addressing these questions. Whether RLI affects the development of other aspects of the hip joint, whether surgical intervention is required, and whether acetabular dysplasia can be reversed after intervention are practical issues that must be addressed urgently. In light of the limitations of our previous study, we aim to address these issues through a retrospective and prospective multicenter randomized controlled study. The main purpose of this study is to clarify the long-term outcome of RLI after DDH closed reduction and its impact on development of the acetabulum. We aim to determine the appropriate indication and timing of surgical intervention for RLI after DDH closed reduction and to provide a basis for revising the acceptable criteria for closed reduction of DDH, to reduce the incidence of OA caused by RAD after DDH treatment.

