##### Exclusion criteria

2.2.1.2.

1.Neuromuscular or syndromic DDH;2.Repeated surgical treatment because of re-dislocation, RAD, or other reason after DDH reduction;3.Incomplete imaging data.

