###### Inclusion criteria

2.2.2.1.1.

Inclusion criteria 1–5 are the same as the previously listed inclusion criteria 1–5 (2.2.1.1);

6. More than 1 year after closed reduction;7. Patients aged ≤5 years at follow-up;8. The magnitude of limbus inversion exceeded 32% of the horizontal depth of acetabular roof at follow-up (or the cut-off value obtained in Protocol 2.2.1);9. The acetabular index was ≤30° at follow-up (since an acetabular index>30° usually necessitates pelvic osteotomy).

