##### Statistical analysis

2.2.2.6.

Fisher's precision probability test was used to compare the difference between the sexes and affected sides, using analysis of variance to compare the different ages between the surgical and non-surgical cohorts. Differences in acetabular index was compared using Student's *t*-test. Chi-square test was used to compare IHDI classification, VAS and HHS, and Severin classification at the final follow-up, and analysis of variance was used to compare the MRI T1ρ mapping values and the incidence of Grade III and Grade IV adverse events.

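### The randomised part names reversal of delayed ossification as a purpose, but it selects on residual limbus inversion and the stated t-test cannot separate reversal from prevention

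*Protocol article*

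**What the plan says.** All references are to the Protocol article.

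- **Purpose.** Section 2.1 (Objectives) includes among its open questions "whether acetabular dysplasia can be reversed after intervention are practical issues that must be addressed urgently". Section 2.2.2.1 explains the choice of children aged 5 years or less by saying that "it is more instrumental to observe the reversibility of delayed acetabular cartilage ossification".
- **Title of the part.** Section 2.2.2 is headed "Effects of RLI clearance on acetabular development: a retrospective and prospective multicenter randomized controlled study", which is broader than reversal.
- **Entry rules.** Section 2.2.2.1.1, item 8: "The magnitude of limbus inversion exceeded 32% of the horizontal depth of acetabular roof at follow-up", or the cut-off found in part 2.2.1. Item 9: "The acetabular index was ≤30° at follow-up (since an acetabular index>30° usually necessitates pelvic osteotomy". Exclusion 2 of section 2.2.1.2, carried over by section 2.2.2.1.2, removes hips with "Repeated surgical treatment because of re-dislocation, RAD, or other reason after DDH reduction".
- **Entry measurement.** Section 2.2.2.1.2 says the acetabular index is assessed in every child who meets the criteria.
- **Analysis.** Section 2.2.2.6: "Differences in acetabular index was compared using Student's" t-test. Section 2.3.1 lists improvement of the index first among the primary outcomes.

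**The concern.** Reversal has a meaning only in a hip whose ossification is already behind for age. The index rule has a ceiling and no floor, and no item asks for delay for age or for lack of progress. A child with marked limbus inversion and an index normal for age can therefore be randomised. In that child a benefit of clearance would be prevention of later dysplasia, not reversal.

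The stated test pools both kinds of hip into one mean difference. A positive result could come from reversal, prevention or both. A null result could mean that clearance does not reverse delay, or that few enrolled hips had any. Part 2.2.2 is the only randomised part, and so the best placed to test reversal of existing delay. Part 2.2.1 is observational, and part 2.2.3 treats at the time of reduction.

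**Working it through.** **1. Purpose, population and test side by side**

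| Element | Where | Content |
|---|---|---|
| Purpose | 2.1, 2.2.2.1 | Reversal of dysplasia or of delayed ossification |
| Population | 2.2.2.1.1, items 8 and 9 | RLI above the cut-off, index at most 30°, no lower or age-referenced limit |
| Test | 2.2.2.6 | One Student's t-test on the index |

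The population matches the section title (effect of clearance on development). It does not match the narrower purpose.

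Section 2.2.2.6 does not say whether the t-test is applied to the final index or to its change from entry. The point holds in either case, because neither version shows how the effect varies with the entry index.

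**2. What the pooled difference estimates**

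Let p be the share of randomised hips not delayed at entry, R the mean effect of clearance in delayed hips (reversal), and P the mean effect in the others (prevention). The t-test estimates

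D = (1 − p) × R + p × P.

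Randomisation makes the estimate of D valid. But D is one number, and R cannot be recovered from it without P. The documents give neither p nor P.

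**3. Can the planning figures size the dilution?**

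The only sample size is in section 2.2.1.4, for the retrospective cohort. It reproduces:

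- Inputs: 21.41 ± 3.61° with RLI, 18.88 ± 4.32° without, alpha 0.05 (taken as two-sided), power 0.9, ratio 1:1, loss 20%.
- Difference: 21.41 − 18.88 = 2.53°.
- Pooled SD: √((3.61² + 4.32²)/2) = 3.98°.
- Evaluable per group: 2 × (3.98 × (1.960 + 1.282)/2.53)² = 52.03, rounded up to 53.
- Enrolled per group: 53/0.8 = 66.25, rounded up to 67, as stated.

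These figures cannot be carried over, for two reasons.

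- They compare hips with and without RLI in another part of the programme. They are not a surgical effect, and section 2.2.2 states no sample size of its own.
- The mean of 21.41° is over all RLI hips, delayed or not, so 2.53° is already a mixed average. Suppose clearance removed the whole difference and acted only in delayed hips. Then R would be 2.53/(1 − p), and D = (1 − p) × 2.53/(1 − p) = 2.53° for any p. Multiplying 2.53° by (1 − p) would count the dilution twice.

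**4. Does RLI imply a raised index?**

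Under a normal distribution, the share of the plan's RLI hips below the no-RLI mean is Φ((18.88 − 21.41)/3.61) = Φ(−0.70) = 0.24. So RLI and a raised index are not the same thing in the plan's own data. The values are from final follow-up, and 18.88° is a group mean, not a limit of normality. The 24% is therefore not an estimate of p at entry.

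**The case against.** The strongest reply is that the trial's question is the titled one, the effect of clearance on development, and that the reversibility phrase only explains the age limit. The overall aim of setting the indication and timing of surgery for RLI needs the effect across RLI hips, including those not yet dysplastic. This stands, and it is why the index entry rule need not change. A reader might infer that the randomised part fails to answer its question. The documents do not support that, because the estimate for hips with RLI is valid.

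A second reply is that hips with a normal index are not hips in which nothing can happen. The Abstract holds that "when limbus inversion exceeds 32.2% of the acetabular depth after closed reduction, RLI persists and leads to RAD", so item 8 selects hips thought to be heading for dysplasia, although the Abstract adds that the evidence was a small cohort with short follow-up. This stands too. Zero effect in non-delayed hips cannot be assumed, and a benefit there would be prevention.

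A third reply is that an analysis by entry index belongs in an analysis plan that is not shown. That is fair against a complaint about a missing subgroup. It does not meet the mismatch in the text, where a purpose, a population and a test are all stated and the test cannot serve the purpose.

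**Conclusion.** The point holds as a mismatch between a stated purpose and the population and test meant to serve it. The randomised comparison validly estimates the effect of clearance in hips with RLI above the cut-off. By itself it cannot support a statement that clearance reverses delayed ossification.

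No size can be put on the mixing. A reader might infer a definite loss of power from the planning values. That would need the share of non-delayed entrants and the effect in them, neither of which is given, and it would dilute a difference that already averages over all RLI hips and was planned for part 2.2.1.

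The conclusion rests on the entry rules being complete as printed and on the entry index being recorded before allocation, as section 2.2.2.1.2 implies. It is a worthwhile, inexpensive improvement and does not invalidate the trial.

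**What to change.** 1. Keep the index entry rule as it is. Separately, the carried-over requirement of more than 5 years of follow-up conflicts with age 5 years or less after reduction at 6–18 months. Those items must be reconciled whatever is done here.
2. In section 2.2.2.6, replace the t-test on the index with a linear model for the follow-up index that includes treatment, entry index and age.
3. Prespecify, before the first 2-yearly comparison, a treatment-by-entry-index interaction in all randomised children, with the entry index continuous and age-adjusted. One form is: follow-up index = b0 + b1 × treatment + b2 × A + b3 × age + b4 × treatment × A, where A is the entry index minus its expected value for age, fitted in the randomised children. The effect at a given A is b1 + b4 × A.
4. Report the overall result as the effect of clearance in hips with RLI. Base any statement about reversal on the estimated effect at a high entry index for age, with its interval.

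The cost is analysis wording only, since entry index and age are already collected. The interaction will have low power, and the reversal estimate a wider interval than the overall effect. In the form shown, high for age is relative to the enrolled children, not to an outside norm. A subgroup cut at an outside age- and sex-specific limit is a more debatable alternative: the documents supply no such limit, and it would use only part of the sample.

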**Figure 5 F5:**
[figure not shown]
Flow diagram of the retrospective and prospective multicenter randomized controlled study.

###### Inclusion criteria

2.2.2.1.1.

Inclusion criteria 1–5 are the same as the previously listed inclusion criteria 1–5 (2.2.1.1);

6. More than 1 year after closed reduction;7. Patients aged ≤5 years at follow-up;8. The magnitude of limbus inversion exceeded 32% of the horizontal depth of acetabular roof at follow-up (or the cut-off value obtained in Protocol 2.2.1);9. The acetabular index was ≤30° at follow-up (since an acetabular index>30° usually necessitates pelvic osteotomy).

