##### Inclusion criteria

2.2.1.1.

1.Pediatric patients undergoing closed reduction at 6–18 months of age;2.No other treatment prior to DDH reduction, with or without the administration of pre-reduction traction or percutaneous adductor tenotomy;3.After DDH reduction, a Spica cast was applied to immobilize the hips in ≤65° of abduction for 3 months, followed by use of abduction braces for 3 months;4.Patients must have a successful closed reduction, defined as a stable reduction enabling femoral head-acetabulum concentricity as suggested by frontal pelvic radiographs taken at 9–12 months after DDH reduction;5.Follow-up for more than 5 years.

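### The randomised part inherits a follow-up criterion of more than 5 years and also caps age at 5 years after reduction at 6–18 months, so no child is eligible as written

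*Protocol article*

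**What the plan says.** Section 2.2.2.1.1 opens the eligibility list of the randomised part with "Inclusion criteria 1–5 are the same as the previously listed inclusion criteria 1–5 (2.2.1.1"), without exempting any item, and continues its own numbering at 6.

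The imported items that matter are in section 2.2.1.1:

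- criterion 1: "Pediatric patients undergoing closed reduction at 6–18 months of age";
- criterion 5: "Follow-up for more than 5 years".

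The added items that matter are in section 2.2.2.1.1:

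- criterion 6: "More than 1 year after closed reduction";
- criterion 7: "Patients aged ≤5 years at follow-up".

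The prose in section 2.2.2.1 describes the same population as children reduced between 6 and 18 months who "had experienced RLI and were ≤5 years old at follow-up were selected as study participants". It justifies the age limit by the ossification potential of acetabular cartilage before age 5 and mentions no 5-year minimum. The Abstract states that "The multicenter retrospective cohort studies required 5 years of follow-up period at minimum" and describes the randomised studies by 6-monthly radiographs and 2-yearly pooling instead. Section 4.1 says that a child must satisfy every inclusion criterion and no exclusion criterion to be considered.

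**The concern.** Criterion 5 suits the retrospective cohort in section 2.2.1, where long elapsed follow-up is the point. Carried into the randomised part, it meets an age ceiling that is no longer than the follow-up it demands. Because reduction takes place some months after birth, a child followed for more than 5 years from reduction is necessarily past that ceiling.

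This is the only randomised comparison in the programme, and it allocates children to arthrotomy or to no surgery. If its entry criteria cannot all hold, every randomised child breaches either criterion 5 or criterion 7, and the list does not say which of the two gives way. The choice matters. If criterion 7 were relaxed, the trial could include children past the age-5 window that section 2.2.2.1 gives as its rationale. That is a possible risk, not a documented outcome.

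**Working it through.** The plan states no figure to reproduce here. The check is eligibility arithmetic on its own criteria.

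**Inputs**

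- Age at reduction, *r*: 6 to 18 months (criterion 1, section 2.2.1.1).
- Time since reduction, *f*: more than 60 months (criterion 5, section 2.2.1.1, inherited).
- Time since reduction, *f*: more than 12 months (criterion 6, section 2.2.2.1.1).
- Age at follow-up: at most 60 months (criterion 7, section 2.2.2.1.1).

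**Formula:** age at follow-up = *r* + *f*.

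**Step 1. Youngest age under criteria 1 and 5**

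- *r* = 6: age > 6 + 60 = 66 months (5.5 years).
- *r* = 18: age > 18 + 60 = 78 months (6.5 years).

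Both exceed the 60 months allowed by criterion 7.

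**Step 2. Longest follow-up under criteria 1 and 7**

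- *r* = 6: *f* ≤ 60 − 6 = 54 months (4.5 years).
- *r* = 18: *f* ≤ 60 − 18 = 42 months (3.5 years).

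Both fall short of the more than 60 months that criterion 5 demands.

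**Step 3. Enumeration.** Taking *r* from 6 to 18 and *f* from 0 to 240 in whole months, the number of combinations that meet criteria 1, 5, 6 and 7 together is 0.

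**Step 4. Other starting points for follow-up.** Counting follow-up from birth does not help: more than 5 years of follow-up would still mean an age above 5 years.

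**Step 5. Redundancy.** *f* > 60 implies *f* > 12, so criterion 5 makes criterion 6 redundant. That a 1-year minimum was written at all suggests that the 5-year minimum was not meant to apply here.

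**Step 6. Same check without criterion 5.** With only *f* > 12 and *r* + *f* ≤ 60, each *r* allows (60 − *r*) − 12 = 48 − *r* whole-month values of *f*. Summed over *r* = 6 to 18, this is 13 × 48 − 156 = 468 combinations. The entry window then runs from just over 12 months after reduction up to 42 months (reduction at 18 months) or 54 months (reduction at 6 months). The remaining criteria are compatible.

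**The case against.** The strongest reply is that the intent can be recovered. Section 2.2.2.1 states the selection rule with its reason and no 5-year minimum, the Abstract attaches that minimum to the retrospective cohort studies, and criterion 6 would be pointless otherwise. A careful reader would conclude that the cross-reference should stop at criterion 4. This stands as evidence of intent and makes the error look like drafting. It does not cure the text: section 2.2.2.1 does not override the numbered list, and section 4.1 requires all criteria to be met.

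A second reply is that criterion 5 might mean follow-up after randomisation, since section 2.2.2.3 plans observation until skeletal maturity. The text does not say so. In section 2.2.1.1 the criterion describes a retrospective cohort, and the randomised part calls its criteria the same. In criteria 7 to 9, follow-up means the assessment at which age, limbus inversion and acetabular index are checked for entry. Future follow-up also could not be verified at enrolment, and using it for inclusion would make inclusion depend on retention after randomisation.

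A third reply is that the article condenses a fuller protocol and that the flow diagram (Figure 5) is not visible here, so the working eligibility list may differ. That limits what can be said about practice at the centres. It does not excuse two stated criteria that contradict each other.

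**Conclusion.** The point holds: criteria 1, 5 and 7 exclude each other in the randomised part, and the eligible set is empty as written. The gap is not marginal. The required follow-up of more than 5 years compares with at most 3.5 to 4.5 years achievable by age 5, a shortfall of more than 0.5 to 1.5 years depending on age at reduction. The result assumes only that criterion 5 means elapsed follow-up at the entry assessment, as it does in section 2.2.1.1. It rests on no outside figure.

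Two stronger readings should be resisted. A reader might infer that the trial will in fact recruit nobody; the documents show only that the written list cannot be satisfied, while the Abstract and section 2.2.2.1 show which population was probably intended. A reader might also infer that centres will each set aside a different criterion; nothing in the documents supports this, and setting aside criterion 7 would contradict section 2.2.2.1 as well.

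This is an internal inconsistency, not a disputed design choice. It must be corrected because it concerns who may be randomised.

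**What to change.** Reconcile sections 2.2.1.1, 2.2.2.1 and 2.2.2.1.1 by changing the cross-reference in section 2.2.2.1.1 so that only criteria 1–4 of section 2.2.1.1 are inherited. Existing criteria 6 and 7 then define the entry window, in agreement with the prose in section 2.2.2.1 and with where the Abstract places the 5-year minimum. No new criterion is needed.

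The cost is a one-line correction to the text, with no additional patients or procedures.

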###### Exclusion criteria

2.2.2.1.2.

Exclusion criteria 1–3 are the same as previously listed exclusion criteria 1–3 (2.2.1.2);
4. Patients who refused inclusion in the study cohorts.For pediatric patients satisfying the inclusion/exclusion criteria, the basic measures of acetabular development including the acetabular index and central-edge angle were assessed using frontal pelvic radiographs; the magnitude of limbus inversion, cartilaginous acetabular index, and T1ρ mapping values were measured using MRI.

##### Randomized blocks and interventions

2.2.2.2.

A randomized trial study design was the most appropriate approach to observe the efficacy of surgical intervention, with blinding techniques used during statistical analysis of the data. A double-blind study was not feasible because the surgeon was required to provide detailed information on the surgical regimen. The researchers in each center divided the RLI participants into two study cohorts based on the randomized block design, i.e., the surgery and non-surgery groups. After informed consent was obtained from the guardians of patients in the surgery group, clearance of the inverted limbus *via* arthrotomy was performed.

All surgeries were performed by pediatric hip joint surgeons with senior job titles *via* a bikini incision, and the inverted limbus tissue embedded between the acetabulum and femoral head was excised after arthrotomy without damaging the limbus-cartilage complex. After surgery, casts or braces were applied to immobilize single hips in abduction for 4 weeks and the patients gradually resumed walking after removal of external fixators. No special rehabilitation therapy was administered.

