##### Bias control

2.2.2.5.

To control bias as much as possible, blinding techniques were adopted for data measurement and analysis, i.e., after the imaging data from each center were summarized into research groups, the grouping of clinical data was blinded to the data measurers; at the same time, a consistency test was conducted on the basic situation of the cohort composition within each center (in the same manner as study protocol 2.2.1) to control bias caused by differences in sample composition at different centers.

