### Research ethics approval

4.1.

The registration of clinical trials was completed prior to this study protocol (registration number: ChiCTR1900020996) and was approved by the Medical Ethics Committee of Shengjing Hospital of China Medical University.

This study will recruit pediatric patients who have undergone closed reduction. Pediatric patients who meet al.l inclusion criteria and do not meet any exclusion criteria will be considered for this study. Prior to enrollment in the study, researchers will explain the objectives and content of the study in detail to the guardians of study participants as well as discuss the surgical risks and benefits of RLI clearance after closed reduction; researchers will ensure that the guardians are fully informed of the study. The guardians of the study participants must provide written informed consent before any research activity may begin. Participation in this study is voluntary and may be withdrawn by the participants' guardians at any time.

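### Section 2.2.2.2 has each centre's researchers allocate children by blocks in an open surgical comparison, and no stated bias control acts before entry

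*Protocol article*

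**What the plan says.** Section 2.2.2.2 (Randomized blocks and interventions) names who allocates and by what method: "The researchers in each center divided the RLI participants into two study cohorts based on the randomized block design". The two groups are surgery and non-surgery. The section adds that "A double-blind study was not feasible because the surgeon was required to provide detailed information on the surgical regimen".

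Masking is described in two places. Section 2.2.2.2 refers to a randomised design "with blinding techniques used during statistical analysis of the data". Section 2.2.2.5 (Bias control) says that, once images from the centres have been brought together, "the grouping of clinical data was blinded to the data measurers", and it adds a consistency check on cohort composition within each centre.

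Entry depends partly on continuous readings. Section 2.2.2.1.1 requires limbus inversion above 32% of the acetabular roof depth (or the cut-off from the first part) and "The acetabular index was ≤30° at follow-up". Section 2.2.2.1.2 excludes "Patients who refused inclusion in the study cohorts".

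Consent appears twice. Straight after the division into groups, section 2.2.2.2 says: "After informed consent was obtained from the guardians of patients in the surgery group, clearance of the inverted limbus" was performed. Section 4.1 says: "The guardians of the study participants must provide written informed consent before any research activity may begin".

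**The concern.** Randomisation balances prognosis only if those who decide whether a child enters cannot tell which arm comes next. Here the text gives the division to local researchers. Because treatment is open, a centre can see which of its earlier children had surgery. If the blocks are filled within a centre, the end of a block may then be deduced.

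Entry also leaves room for judgement: two imaging cut-offs, and the guardian's decision after counselling. If the next arm were foreseeable, a child close to 32% or 30° could be read in or out, or a guardian counselled differently, according to that arm. The variables affected would be prognostic, because improvement of the acetabular index is a primary outcome (2.3.1) and the index is itself an entry measurement. Section 2.2.2.6 compares the index by Student's t-test, which would not correct a baseline imbalance. Masking the measurer or the analyst afterwards cannot undo selection that has already happened.

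The consent wording adds to the exposure. If a guardian's decision comes after the arm is known, a refusal prompted by the arm could count as an exclusion.

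**Working it through.** **No figure of the plan applies.** The only sample size, 67 per group in section 2.2.1.4, belongs to the retrospective first part. It reproduces (53 per group before losses; 53 / 0.8 = 66.25, rounded up to 67) but does not bear on allocation in the randomised part.

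**1. Which safeguard acts when**

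| Stated safeguard | Section | Acts before the arm is assigned? |
|---|---|---|
| Blinding during statistical analysis | 2.2.2.2 | No |
| Measurers masked to group on pooled images | 2.2.2.5 | No: at eligibility there is no group yet to mask |
| Consistency check of cohort composition | 2.2.2.5 | No: it describes children already included |

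**2. How much could be foreseen**

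Assumptions, none of them stated for this part: children enter sequentially; blocks are permuted and 1:1; block size is fixed and known at the centre; past assignments are visible. The last follows from open treatment. A 1:1 ratio is stated only for the sizing of the first part.

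Take a block of size 2m, with m children per arm. Once one arm is used up, all remaining places are certain, so the deducible part is the final run of a single arm. The m places of one arm split the m places of the other into m + 1 gaps, so the expected number after the last place of the first arm is m/(m + 1). The same holds with the arms exchanged, and only one of the two can be non-zero in any block. Hence:

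- expected deducible places per block = 2m/(m + 1)
- share of all assignments = [2m/(m + 1)] / 2m = 1/(m + 1)

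Check for blocks of 4: AABB has a final run of 2, ABAB of 1 and ABBA of 1, and the three mirror images match. The share is (2 + 1 + 1)/(3 × 4) = 4/12 = 33.3%.

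The last column below gives the share guessed correctly by always naming the arm with more places left. It comes from enumerating every block. For blocks of 4 it is (1/2 + 2/3 + 2/3 + 1)/4 = 70.8%.

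| Block size | m | Known with certainty, 1/(m + 1) | Guessed correctly |
|---|---|---|---|
| 2 | 1 | 50% | 75% |
| 4 | 2 | 33.3% | 70.8% |
| 6 | 3 | 25% | 68.3% |
| 8 | 4 | 20% | 66.6% |
| 10 | 5 | 16.7% | 65.3% |

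Under full concealment the correct-guess share would be 50%.

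**3. The consent statements side by side**

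Section 4.1 places written guardian consent before any research activity, for all participants. Section 2.2.2.2 mentions consent once, after the division, and for the surgery group alone. Read alone, section 2.2.2.2 allows the arm to be known before consent; section 4.1 does not.

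**The case against.** The strongest objection is that one condensed sentence carries the point. A journal article commonly leaves sequence generation, block size and concealment to the full protocol, which is not shown. Site staff can also carry out allocation from sealed envelopes or a central list, and the sentence fits that. This stands as a limit: a reader might infer that assignments could in fact be foreseen, or that enrolment was steered, and the article supports neither. What remains is that the article does not merely omit the procedure. It states that local researchers made the division, and the safeguards it lists all come later.

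A second objection is that the mechanism needs sequential entry into permuted blocks. The children are selected at follow-up after an earlier reduction, so an eligible pool might be assembled first and divided afterwards, or the blocking might be on centre or baseline features. If the pool were fixed before allocation, there would be no next assignment to foresee. This also stands, and it is why the percentages are conditional.

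Third, the article does not say that the same people screen, counsel and allocate; that is an inference. Section 2.2.1.3 provides two raters per parameter with a reliability assessment, and section 2.2.2.3 carries the parameters into this part. Two raters make it harder for one reader to steer entry, but they do not conceal the sequence.

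Finally, the consent in section 2.2.2.2 may be consent to the operation rather than to the trial. A reader might infer that non-surgery children were enrolled without consent; section 4.1 says otherwise. The two sections still need to be made to agree on timing.

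**Conclusion.** The point holds as a weakness in the stated allocation procedure. Section 2.2.2.2 gives the division between surgery and non-surgery to each centre's researchers, by blocks, in an open comparison, and no control described in 2.2.2.2 or 2.2.2.5 acts before entry. Between 16.7% (blocks of 10) and 50% (blocks of 2) of assignments would be certain in advance, provided entry is sequential and blocks are 1:1, of fixed size and known to the centre. No bias in the acetabular index can be calculated from the documents, and selective entry is a risk rather than a shown event. The difference in consent timing between 2.2.2.2 and 4.1 is a separate matter of wording that should be settled with it.

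**What to change.** Change section 2.2.2.2 as follows:

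- A person independent of both the centres and the blinded analysis team holds a computer-generated list, stratified by centre, with varying block sizes not disclosed to the centres. The central database administration named in section 4.2 is one possibility. The independent statistical team is not suitable: 4.2 describes it as receiving locked files for analysis, and holding the list could undo the blinding that 2.2.2.2 relies on.
- Centre researchers enrol but do not allocate. The arm is released only after the eligibility readings and guardian consent, for children in both arms, are recorded and locked.
- Reconcile sections 2.2.2.2 and 4.1 on when consent is taken and from whom.

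If concealed allocation of this kind is already in place, a sentence in 2.2.2.2 saying so, together with the consent correction, is enough.

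The cost is modest: a small set-up task, since section 4.2 describes a registration system but no randomisation function; a short wait per child for release of the arm; and slightly looser balance within centres from varying blocks. Sample size, treatments and outcomes do not change.
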